**Fig. 1 Fig1:**
[figure not shown]
PRAISE-2 study process overview

### Study location and clinical sites

The PRAISE-2 Methods Centre will be located at McMaster University’s Centre for Evidence-Based Orthopaedics. The Centre for Evidence-Based Orthopaedics is a well-established research group specializing in large-scale multicentre trauma trials and observational IPV studies. Clinical sites that will enroll patients for the PRAISE-2 pilot study include the Hamilton General Hospital in Hamilton Ontario, St. Michael’s Hospital in Toronto Ontario, Foothills Medical Centre in Calgary Alberta, Deventer Hospital in Deventer the Netherlands, University Hospital Vall d’Hebron in Barcelona Spain, and Hospital District of Helsinki in Helsinki Finland. All recruiting sites have worked with the Methods Centre previously on at least one large-scale multinational trauma trial and/or IPV study.

### Protecting against sources of bias

#### Ensuring protocol adherence

Prior to starting the study, site investigators and study personnel will attend an investigators meeting, either in-person or by teleconference, to review the study protocol and discuss enrollment and adherence strategies. The Methods Centre will send out regular study newsletters to each clinical site updating them on the overall study progress, summarizing their clinical site’s progress, and thanking them for their continued support. Study personnel will keep daily records of all patients that were eligible but not enrolled in the study (missed) and the reason why. Study personnel will record this information on the case report forms and submit them to the McMaster University-based Methods Centre on a regular basis. Methods Centre personnel will contact any centres with high rates of missed patients to discuss procedures and to establish solutions to any problems. Sites will receive regular quality control reports from the Methods Centre.

#### Ensuring data quality

All study personnel will participate in a training session prior to study commencement to ensure consistency in study procedures, including data collection and reporting. Site investigators can contact the Methods Centre at any time to resolve any problems or questions that arise. We will use an electronic data collection system with quality and logic checks, supplemented with regular manual data quality checks. Study personnel at the Methods Centre will review data for completeness and quality from clinical sites daily. The Methods Centre personnel will follow-up with quality control reports on a regular basis.

#### Maximizing patient follow-up

As previous studies have reported high loss to follow-up rates with IPV victims [35], we will implement a strategy designed to minimize loss to follow-up adapted from Logan et al. [36] (Fig. 2) to reduce bias associated with loss to follow-up. Logan et al. were able to achieve nearly a 75% recruitment rate and a 94% follow-up rate after 1 year in a population of severely abused women [36]. We have previously used the majority of these strategies to maximize follow-up in multicentre studies [37]. Main features of this strategy include (1) excluding individuals who are very likely to present problems with follow-up; (2) prior to leaving the surgical clinic, as well as their own telephone number, each patient will provide the name and address of alternate contacts who are likely to be aware of the patient’s whereabouts; (3) patients will receive a reminder card for their next follow-up visit from the clinical research coordinator; and (4) follow-up visits will coincide with standard fracture clinic visits. Alternatively, patients can complete the major study questionnaires over the phone.

**Fig. 2 Fig2:**
[figure not shown]
PRAISE-2 enrolment and follow-up enhancement strategies

#### Identifying IPV status

A bias toward under-reporting IPV is possible with the self-reporting nature of identifying IPV; however, we were able to elicit a disclosure of abuse in the past year from one in six women in the original PRAISE study which is similar to estimates of IPV in other specialties. Our previous studies show that our method of identifying IPV victims is more sensitive than other common methods of identifying IPV [28]. Because of this, we are confident in our ability to correctly identify the majority of IPV victims. Considerations with respect to confidentiality will be addressed during data collection to reduce bias when participants are completing the questionnaire. Participants will be approached by a female research coordinator, and the consent process and the completion of the questionnaires will take place alone in a private location to reduce influence from others. A female research coordinator is used to make the participant feel safer and more comfortable with disclosure. In our POSITIVE study [38], we found that 82% of female fracture clinic patients would prefer to speak to a female about IPV.

#### Independent blinded adjudication

An independent adjudicator blinded to patients’ IPV status will review radiographs and clinic notes to confirm injury-related complications where necessary.

### Statistical plan

#### Sample size determination

The sample size for the pilot study is primarily based on feasibility considerations. Based on data from the original PRAISE study, 1 in 3 women presenting to fracture clinics have a lifetime history of IPV, 1 in 6 have a history of IPV in the past year, and 1 in 50 women present to fracture clinics because of an IPV-related injury [14]. Based on the statistic that 1 in 50 women present to fracture clinics because of an IPV-related injury, we aim to recruit 50 women at each of 5 sites (250 total). We determined a priori that the study will be feasible if loss to follow-up is less than 15% and adherence to study windows is 75% or greater. We believe that our loss to follow-up will be about 10%; therefore, using the confidence interval approach suggested by Thabane et al. [39], we require 214 patients to achieve a 5% margin of error (which will generate a confidence interval that excludes 15%). We believe that the adherence to study windows will be over 80%; therefore, we require 214 patients to achieve a 6% margin of error (which will generate a confidence interval that excludes 75%). Therefore, 250 participants will be sufficient to assess our feasibility outcomes. We intend to use data from the pilot study to inform the definitive sample size calculation.

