**Methods:**

We will complete a pilot multicentre prospective cohort study of 250 women with musculoskeletal injuries to determine the feasibility of a multinational prospective cohort study that will determine if prior or ongoing IPV affects orthopaedic outcomes following an injury, and how patterns of IPV change over time. Our primary outcome is feasibility measured using recruitment rate (success criterion 50 patients/site in 12 months), adherence to visit windows (success criterion 75%), participant retention (success criterion 85%), and data completeness (success criterion 80%). Our secondary exploratory clinical outcomes are injury-related complications, return to function, new IPV disclosures, utilization and cost of support services, changes in abuse patterns, quality of life, and readiness to make relationship changes. We will assess feasibility based on pre-defined criteria for feasibility success and we will analyze secondary outcomes in an exploratory fashion.

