### Overview of the design

We plan to complete a multicentre pilot prospective cohort study of 250 women with musculoskeletal injuries to assess our ability to recruit and follow our target population, and to measure our clinical outcomes.

Important design and organizational aspects of the proposed PRAISE-2 study include (1) leveraging the international interest in IPV in surgical settings from the original PRAISE study to strengthen buy-in for this pilot cohort study; (2) broad eligibility criteria (all adult females with musculoskeletal injuries who are able to provide informed consent in a private location) ensures wide applicability of our findings beyond the centres involved; and (3) a comprehensive plan to maximize follow-up rates while maintaining patient safety.

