### Study outcomes

#### Primary (feasibility) outcomes

The primary outcome of the pilot study is feasibility including recruitment, adherence to visit windows, participant retention, and data completeness. The criteria for success of feasibility are as follows:Recruitment—Our recruitment strategy will be considered feasible if each site is able to recruit 50 participants in 12 months or less after their training call/visit.Adherence to visit windows—We have attempted to align study visit windows with clinical standard of care visits; however, standard of care visits can vary by region and/or type of injury. We expect that at least 75% of study visits should be within the defined windows in Table 1.Participant retention—While 20% loss to follow-up has traditionally been considered the industry standard [26], there is evidence from orthopaedic studies that bias begins to affect study results at even lower rates of loss to follow-up [27]. Therefore, our loss to follow-up minimization strategy will be considered feasible if loss to follow-up remains under 15%.Data completeness—Based on our experience in previous multicentre orthopaedic trauma studies, we are typically able to obtain questionnaire completeness rates of 75–85% at 12 months. Therefore, we will consider our data collection strategies to be feasible if questionnaire completion remains over 80%.

**Table 1 Tab1:** PRAISE-2 schedule of events

Assessment	Baseline (0–6 weeks from injury)	1 month (2–6 weeks from injury)	3 months (11–15 weeks from injury)	6 months (24–28 weeks from injury)	12 months (48–56 weeks from injury)
Target visit window					
Screening form	X				
Informed consent	X				
Demographic characteristics form	X				
Injury characteristics form	X				
IPV status (type, frequency, severity)	X	X	X	X	X
Assessment for complications	X	X	X	X	X
Support service utilization	X	X	X	X	X
Return to function	X	X	X	X	X
EQ-5D	X	X	X	X	X
Stages of change	X	X	X	X	X
Radiograph	(X)	(X)	(X)	(X)	(X)
Clinic notes	(X)	(X)	(X)	(X)	(X)

(X) = Only if required to adjudicate an adverse event

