#### Primary analysis

A summary of objectives, outcomes, and analyses is presented in Table 3. We will report feasibility outcomes descriptively by site as proportions with 95% CIs. We will also report whether each feasibility outcome met the criteria for feasibility success.

**Table 3 Tab3:** Summary of objectives, outcomes, success criteria, and analyses

Primary			
Objective	Outcome	Success criteria	Analysis
Feasibility	Recruitment	Each site should recruit 50 participants in 12 months or less	Descriptive—proportions with 95% CI
	Adherence to visit windows	At least 75% of study visits should be within the defined windows	
	Participant retention	Loss to follow-up should remain under 15%	
	Data completeness	Questionnaire completion rates should remain over 80%	
Secondary			
Objective	Outcome	Analysis	
Determine how a history of IPV affects injury-related complications	Injury-related complications	Proportions of patients experiencing injury-related complications by group with 95% CI; logistic regression.	
Determine how a history of IPV affects return to pre-injury function	Return to pre-injury function	Proportion of patients achieving return to pre-injury level of function in each group at baseline, 3 months, 6 months, and 12 months with 95% CI; logistic regression.	
Determine incident cases of IPV	New IPV disclosures	Incidence statistic with 95% CI.	
Determine how a history of IPV affects health care and support service use	Utilization and associated costs of support services and hospitalizations	Proportions of women using each service per group over 12 months, median number of times that participants used each service with IQR. Estimated mean costs with 95% CI in each group and bootstrap differences between those with a history of IPV and those without with 95% CI.	
Determine how patterns of IPV change over time	Changes in abuse severity/frequency and type	Proportion of patients who experienced no abuse, a stable level of abuse, escalating abuse, and de-escalating abuse over 12 months with 95% CI; graphically.	
Determine how a history of IPV affects HRQL after a musculoskeletal injury	EuroQuol-5 Dimensions (EQ-5D)	Mean change in HRQL from baseline to the 3 month, 6 month, and 12 month visits, by group with 95% CI.	
Determine how abused women’s stage of change changes over time	Domestic Violence Survivor Assessment (DVSA)	Change in stage of change from baseline at 3 months, 6 months, 9 months, and 12 months.	

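### Six enrolling sites are named, but the total of 250 assumes five sites of 50, so the requirement that each site recruit 50 does not fit the stated sample size

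*Protocol article*

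**What the plan says.** All places are in the protocol article.

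- **Sample size determination** builds the total from sites: "we aim to recruit 50 women at each of 5 sites (250 total").
- **Overview of the design** repeats the total: "We plan to complete a multicentre pilot prospective cohort study of 250 women with musculoskeletal injuries". The Methods paragraph of the Abstract also gives 250.
- **Study location and clinical sites** begins "Clinical sites that will enroll patients for the PRAISE-2 pilot study include the Hamilton General Hospital in Hamilton Ontario" and goes on to Toronto, Calgary, Deventer, Barcelona and Helsinki. That makes six. The section then refers to them all as recruiting sites.
- **Primary (feasibility) outcomes** sets the criterion: "Our recruitment strategy will be considered feasible if each site is able to recruit 50 participants in 12 months or less after their training call/visit".
- **Table 3**, under Primary analysis, restates it: "Each site should recruit 50 participants in 12 months or less".
- The **Abstract** words it as "recruitment rate (success criterion 50 patients/site in 12 months").

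Nowhere is one of the six described as a reserve or replacement site, or as sharing a target with another. Nothing says whether enrolment closes at 250 or may run past it.

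**The concern.** Feasibility is the primary objective, and recruitment is the first of its four pre-defined success criteria. The Primary analysis section commits to reporting whether each criterion was met. The recruitment criterion applies to every site, so the number of sites fixes how many women are needed to satisfy it. The total was set for five sites and the site list has six.

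If the study closes at 250 with all six sites enrolling, the recruitment result would reflect the mismatch and not how well the sites recruited. The team would then have to decide, with the counts in view, which sites to judge or how to score a site that closed early. A pre-defined criterion is meant to prevent that kind of choice, and this result is intended to inform the definitive study.

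**Working it through.** **Inputs**

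- Per-site target: 50 in 12 months (Primary (feasibility) outcomes; Table 3).
- Sites assumed in the total: 5 (Sample size determination).
- Sites named: 6 (Study location and clinical sites).
- Stated total: 250 (Abstract; Overview of the design; Sample size determination).

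**Step 1. Reproduce the plan's figure.** Total = sites × target = 5 × 50 = 250. The stated total is reproduced exactly, so the multiplication is sound.

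**Step 2. Use the six named sites.** 6 × 50 = 300. The gap is 300 − 250 = 50 women, and 300/250 = 1.20, so the criterion needs 20% more than the stated total.

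**Step 3. Hold the total at 250.**

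- Mean per site: 250/6 = 41.7.
- Most sites that can reach 50: 250/50 = 5, which leaves none for the sixth.
- If every site enrols at least one woman, five sites at 50 plus one more is 251, which exceeds 250. At most four sites can then reach 50.

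**Step 4. Does faster recruitment help?** The target pace is 50/12 = 4.17 per site per month. As an illustration, suppose all six sites open together and recruit at exactly that pace. They enrol 6 × 50/12 = 25 per month and reach 250 at 250/25 = 10 months, with 41.7 each. At twice the pace they reach 250 at 5 months, again with 41.7 each. Under a cap, speed changes the closing date but not the number of women available per site.

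**Step 5. Effect on the other feasibility outcomes.** The half-width of a simple 95% interval is 1.96 × √(p(1 − p)/n), taken at the section's expected values of 10% loss to follow-up and 80% adherence.

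| n | p = 0.10 | p = 0.80 |
|---|---|---|
| 250 | 3.7% | 5.0% |
| 300 | 3.4% | 4.5% |

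Both totals exceed the 214 that the section says it needs for these two outcomes, and moving to 300 only narrows the intervals. The derivation of 214 is a separate matter and nothing here relies on it.

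**The case against.** The strongest reply is that 250 is a target and not a ceiling. The sample size section speaks of an aim, calls 250 sufficient, and asks for only 214 on precision grounds. No closing rule at 250 is stated. Without one, six sites could each enrol 50 and the study would finish at 300, with no harm to inference in an observational questionnaire cohort. This stands, and it makes the impossibility conditional. It does not remove the conflict, because 300 appears nowhere and would contradict the total given in three places.

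A second reply is that the criterion already has the sense of a rate. The Abstract calls it a recruitment rate, and the outcomes section asks whether a site is able to recruit 50 within 12 months of its own training call. A site on pace when the study fills is not plainly a failure on that wording. This stands in part. Table 3 reads more strictly, as 50 actually enrolled, and neither place says how a site closed early is scored.

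A third reply is that results are reported descriptively by site, so each site's recruitment would be visible, and no automatic decision rests on recruitment alone. That is fair and limits the severity. The plan still commits to a met-or-not-met statement for this criterion.

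It could also be said that a journal article condenses the full protocol. That explains omissions, but here two explicit statements in the same article disagree.

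**Conclusion.** The inconsistency is real. Six sites are named, the total rests on five, and the primary recruitment criterion applies to each site. With six sites it needs 300 women against a stated 250, a gap of 50 or 20%. If enrolment stops at 250, the mean is 41.7 per site and the criterion cannot be met at all six.

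This rests on two assumptions: that all six named sites enrol, as the article says, and, for the impossibility, that 250 is a cap, which the article neither states nor rules out.

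A reader might infer that the study is bound to be declared infeasible on recruitment. The article does not support that, because it contains no rule closing enrolment at 250. A reader might also infer that the sample size is miscalculated or too small for its purpose. It is not shown to be: 5 × 50 = 250 is correct, and the precision of the retention and adherence estimates does not suffer at 250 or at 300. The fault is an internal inconsistency between the site count, the total and a primary success criterion. It should be fixed, but it does not undermine the rest of the plan.

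**What to change.** Make the site count and the total agree in the Abstract, Overview of the design, Study location and clinical sites, and Sample size determination. Either of these is coherent:

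1. Five sites and 250, with the site list changed to match.
2. Six sites and 300.

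In either case, say whether the total is a cap.

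If six sites are kept with 250 as a cap, add a rule to Primary (feasibility) outcomes and to Table 3 before data are seen. A site closed early because the study is full would be judged on its pace against 50 per 12 months (about 4.2 per month) over the time it was open, and would not be counted as a failure. The rule needs a minimum open time, chosen in advance, so that a briefly open site cannot pass on a handful of participants.

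The first option and the capped six-site option cost only wording and add no participants. The second adds 50 women with 12 months of follow-up each. The pace rule has a small downside: a shortened site is judged on its rate and not on 50 women actually enrolled.

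### The adherence sample-size statement contradicts itself (80% minus a 6-point margin is 74%, which does not exclude 75%), and 214 patients does not follow from both sets of stated inputs

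*Protocol article*

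**What the plan says.** The section Sample size determination sets the two criteria: "the study will be feasible if loss to follow-up is less than 15% and adherence to study windows is 75% or greater". It then gives a planning value and a requirement for each.

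- Loss to follow-up: "We believe that our loss to follow-up will be about 10" per cent, and so "we require 214 patients to achieve a 5% margin of error (which will generate a confidence interval that excludes 15" per cent.
- Adherence: "We believe that the adherence to study windows will be over 80" per cent, and so "we require 214 patients to achieve a 6% margin of error (which will generate a confidence interval that excludes 75" per cent.

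It concludes: "Therefore, 250 participants will be sufficient to assess our feasibility outcomes". The method is attributed to a cited reference. No interval formula and no allowance for dropout is stated. The confidence level appears only under Primary analysis: "We will report feasibility outcomes descriptively by site as proportions with 95% CIs". Table 3 in that section defines the adherence criterion by visits: "At least 75% of study visits should be within the defined windows".

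**The concern.** Two different problems, 10% with a 5-point margin and 80% with a 6-point margin, are given the same answer. The adherence promise also fails on subtraction alone, because the threshold is 5 points below the planning value and the margin is 6 points.

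Feasibility is the primary outcome, and this paragraph is the only precision argument offered for it. A reader is told without condition that the adherence interval will clear its threshold, and that 250 women are sufficient for that reason. On the stated figures this assurance does not hold at the planning value.

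**Working it through.** **Inputs.** From Sample size determination: 10% loss, 5-point margin, threshold 15%; adherence over 80% (80% is the only number given), 6-point margin, threshold 75%; n = 214 for both; planned N = 250. From Primary analysis: 95% confidence, taken here as two-sided, so z = 1.96.

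**1. Does 214 reproduce?** The usual formula is n = z² p(1 − p)/m².

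- Loss: 3.8416 × 0.09 / 0.0025 = 138.3, so 139.
- Adherence: 3.8416 × 0.16 / 0.0036 = 170.7, so 171.

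Other methods, requiring the farther limit to lie within the stated margin:

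| Method | Loss, 10% ± 5 | Adherence, 80% ± 6 |
|---|---|---|
| Wald | 139 | 171 |
| Wald, continuity-corrected | 158 | 188 |
| Wilson | 196 | 206 |
| Clopper-Pearson | 202 | 214 |
| Wilson, continuity-corrected | 216 | 222 |
| Wald, inflated for 20% dropout | 139/0.80 = 174 | 171/0.80 = 214 |

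The adherence figure alone can be reached in two ways, neither of them stated. Neither gives 214 for loss to follow-up. Other confidence levels, one-sided limits and one-sample tests were also tried, and none gave 214 for both.

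**2. Does the stated adherence margin exclude 75%?** 80 − 6 = 74 and 80 + 6 = 86, so 75% lies inside. For the lower limit to pass 75% with a 6-point margin, the observed rate must exceed 75 + 6 = 81%.

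**3. Does n = 214 rescue it?** Treating adherence as one proportion per patient, as the calculation does, the margin at 80% is 1.96 × √(0.16/214) = 5.36 points.

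- Wald: 74.6% to 85.4%
- Wilson: 74.1% to 84.8%
- Clopper-Pearson: 74.0% to 85.1%

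All three contain 75%. With Wald limits the observed rate must be above about 80.3%, that is at least 172/214 = 80.4%.

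**4. Loss to follow-up.** The nominal margin gives 10 + 5 = 15, which touches the threshold. The margin that 214 patients deliver is 1.96 × √(0.09/214) = 4.02 points, or 6.0% to 14.0%. The Wilson and Clopper-Pearson upper limits at 10% are 14.75% and 14.8%. All exclude 15%. With 250 women the margin is 1.96 × √(0.09/250) = 3.72 points, or 6.3% to 13.7%.

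**5. Unit of the adherence criterion.** The criterion counts study visits, while the calculation counts patients. Assume four follow-up visits per woman (1, 3, 6 and 12 months, under Study follow-up), full attendance, and a within-woman correlation ρ. The documents give no ρ, so a range is shown. The effective number is 4 × women / (1 + 3ρ). Wald margins at 80%:

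| ρ | 214 women | 250 women |
|---|---|---|
| 0 | 856 effective, 2.7 points | 1000 effective, 2.5 points |
| 0.5 | 342 effective, 4.2 points | 400 effective, 3.9 points |
| 1 | 214 effective, 5.4 points | 250 effective, 5.0 points |

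A margin under 5 points needs more than 3.8416 × 0.16 / 0.0025 = 245.9 effective observations. With 214 women that holds for ρ below (856/245.9 − 1)/3, about 0.83.

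**The case against.** The strongest reply has four parts.

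- **The article says adherence will be over 80%, not exactly 80%.** This stands as far as it goes. At n = 214, an observed 81% gives a patient-level Wald lower limit of 75.7%, and 82% gives 76.9%. But no value above 80% is stated, and the promise is unconditional.
- **214 exceeds both 139 and 171, so the study is not short of patients for its stated margins.** This is correct, and no increase is called for.
- **The success criteria are thresholds.** Nothing in the article makes success depend on an interval excluding one. This also stands, and it limits the consequence to the justification of the sample size.
- **The cited method may explain 214.** It could for adherence alone, through an exact interval or a 20% inflation. It would still not explain the pair.

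A reader might infer three stronger points that the documents do not support.

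- **That the loss-to-follow-up claim is false too.** Only the nominal margin touches 15%; the stated n excludes it at an observed 10%.
- **That at least 246 patients are needed, or that 250 only just suffices for adherence.** Those figures describe a patient-level proportion, whereas the criterion is a share of visits. On visits, 250 women may give a clearly narrower interval.
- **That the plan fails because 50 women per site give wide intervals.** Site reporting is described as descriptive and no site-level precision is promised. Whether the pooled or the site figure is judged is a separate clarification.

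**Conclusion.** The point holds in a limited form. The adherence sentence is wrong at the only planning value given: the stated margin yields 74% to 86%, and 214 patients yield 74.6% to 85.4% at patient level, so 75% is not excluded. Exclusion needs an observed rate above 81% with the stated margin, or above about 80.3% with the Wald margin at 214. The first of these results is plain subtraction and depends on no method. The others assume two-sided 95% limits and one observation per patient.

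The requirement of 214 for both outcomes is unexplained: the usual formula gives 139 and 171, and no single method tried gives 214 twice. For loss to follow-up the conclusion is sound at an observed 10%, although the quoted 5-point margin is not the margin that secures it.

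The fault lies in the stated justification. It does not show that 250 women are too few, and it changes no analysis or success criterion.

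**What to change.** Revise the two sentences in Sample size determination as follows.

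1. Name the interval method, the confidence level and any dropout allowance.
2. Replace 214 with figures that follow from the inputs. With the usual 95% formula, 10% ± 5 points needs 139 women, and 80% ± 6 points needs 171 independent observations.
3. State what 250 women give for loss to follow-up: about 3.7 points at 10% (6.3% to 13.7%).
4. Delete the unconditional claim that the adherence interval will exclude 75%, or replace it with the observed rate needed to exclude it.
5. Compute adherence precision on study visits, allowing for several visits per woman, with the within-woman correlation stated as an assumption and shown over a range.

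The cost is wording and a short recalculation, with no more patients. The downside is that the assurance given to the reader becomes conditional on the adherence observed and on the assumed correlation.
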